### Sample size estimation

The primary analyses will compare: (A) the primary outcome 1 (rate of traditional smoking sustained cessation) across the groups TC, Mixed and EC (only the subjects that were former traditional smokers); (B) the difference in the number of traditional cigarettes smoked per day between baseline and end of follow-up in groups TC and Mixed.

As regards primary analysis 1, conservatively assuming a 5-year cessation rate of 20% in the TC group, and 30% in the Mixed group (EC group most probably having a higher cessation rate), we would need 313 subjects per group to achieve a power of 80%. Given the need of multivariate modeling and an expected 20% rate of withdrawals/dropouts, 500 subjects would be required in each group.

Concerning primary analysis 2, assuming a 5-year reduction in the number of smoked traditional cigarettes of 2 ± 6 and 4 ± 6 in the Mixed group, with the same above parameters (alpha error = 0.05; beta-error = 0.20; dropout/withdrawals = 20%), we would only require 240 subjects per group.

We will thus conservatively enroll a minimum of 500 subjects in each group (EC, TC and Mixed), for a total of 1500 participants.

### Data analysis

All data will be collected and initially handled by the Coordinating unit, which is responsible for privacy regulations and maintains the property.

At each time-point, the differences in the rates of traditional smoking cessation (or other categorical outcomes such as adverse events) across groups will be first examined using Fisher’s exact test. Cox proportional hazards analysis will be used to calculate the adjusted relative hazards of traditional smoking cessation (and smoking-related hospitalization) by each variable. Stochastic level of entry into the model will be set at 0.10, with age, gender, and smoking groups forced to entry, and multicollinearity, interactions with time to event and higher-power terms will be explored for all variables in the final model. A minimum events-to-variable ratio of 10 will be maintained in multivariate modeling to avoid overfitting, and Schoenfeld’s test will be performed to check the validity of proportional hazards assumption. Kaplan-Meier survival analysis will also be used to examine the association between hospitalization and smoking group. The validity of constant incidence ratios over the follow-up will be checked using Nelson-Aalen cumulative hazard estimates.

Multiple linear regression will be used to investigate the predictors of the difference in the number of traditional cigarettes smoked between baseline and each time-point of follow-up. Additional multivariate models such as mixed-effect logistic models will be explored for both the primary and secondary outcomes to account for repeated observations and the potential distortions of the variability in the exposure to traditional cigarette smoking by the participants in groups EC and Mixed (for which also stratification will be considered) [31]. In all mixed models, the cluster variables will be participant’s id, nicotine level of the electronic and traditional cigarette and exposure to past traditional cigarette smoking. We will assume and independent correlation structure for all clusters, but we will also repeat all models setting an exchangeable correlation structure.

The prevalence of e-cigarette smoking compliance (secondary outcome n. 1) will similarly be derived at 6, 12, 24, 36 and 60 months. However, with the exception of the 6-months cut-off (which will probably include the vast majority of participants), the crude estimates of adherence for the following time-points would most probably be underestimated, as several participants who are still adherent will be excluded because they will not be followed up to the cut-off point. Therefore, adjusted estimates of adherence for each follow-up point will be calculated using the Nelson-Aalen method for censoring, which assigns censored observations according to the corresponding period of failure incidence [32].

A p-value of <0.05 will be considered significant for all analyses, which will be performed using STATA statistical software, version 11.1 (Stata Corporation, College Station, TX, USA, 2007).

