### Interventions and groups

This is a non-interventional observational study. The participants will be divided into three cohorts/groups according to their self-determined smoking pattern:

– Group EC - smokers of e-cigarettes only (who are not smoking traditional cigarettes). This group will be further split in the analysis: never or former smokers of traditional cigarettes; smokers of e-cigarettes with or without nicotine.

– Group TC - smokers of traditional cigarettes only. This group will be further split in the analysis: recent and older smokers.

– Mixed Group - smokers of both traditional and electronic cigarettes. This group will be further split in the analysis: mixed smokers who quit and who did not quit traditional cigarette smoking during follow-up.

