### Questionnaire

The structured questionnaire is available as online supplementary material and contains questions on demographic data (gender, age, height and weight, educational level, marital status, occupation), previous diseases which are and are not among the reasons for the exclusion, smoking habits, smoking related diseases which did or did not require hospitalizations (only in follow-up assessments), lifestyle behavior (physical activity, alcohol use) and quality of life. The latter issue will be investigated using the Italian version of the validated EuroQol EQ-D5L questionnaire [29]. The questionnaire will be kept as short as possible to allow phone interviews and will be initially tested on a sample of 50 participants to assess acceptability, exclude potentially redundant or include potentially useful questions.

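### With self-selected groups, the Cox model for cessation leaves every confounder except age and gender to a p<0.10 entry rule, and the time-point cessation test is unadjusted, so baseline differences can stay in the comparison.

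*Protocol article*

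**What the plan says.** The section Interventions and groups forms "three cohorts/groups according to their self-determined smoking pattern". Nothing is allocated, so the groups may differ at baseline in anything related to quitting.

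The Data analysis section then takes three steps for cessation:

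- At each time-point, differences in cessation rates "across groups will be first examined using Fisher’s exact test". This test takes no covariates.
- "Cox proportional hazards analysis will be used to calculate the adjusted relative hazards of traditional smoking cessation". The covariate rule for this model is: "Stochastic level of entry into the model will be set at 0.10, with age, gender, and smoking groups forced to entry". It is bounded by a further condition: "A minimum events-to-variable ratio of 10 will be maintained in multivariate modeling to avoid overfitting".
- "Additional multivariate models such as mixed-effect logistic models will be explored for both the primary and secondary outcomes".

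The section ends by applying a 5% significance threshold to every analysis. It does not say which cessation result decides the primary question.

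The Questionnaire section shows that education, marital status, occupation, previous diseases, smoking habits, physical activity and alcohol use are all collected. The Sample size estimation section sizes the study on 5-year cessation of 20% (TC) against 30% (Mixed).

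**The concern.** A covariate's p-value for the outcome does not measure how much it distorts the group contrast. A variable that differs clearly between groups but has a modest link with quitting can fail the 0.10 screen and still bias the hazard ratio, and several such variables can add up. The screen suits prediction better than confounder control.

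The crude time-point test has the larger exposure. It addresses the quantity the study is sized on, removes no baseline difference, and falls under the same 5% threshold as the adjusted models. If Mixed users are, for instance, better educated or lighter smokers than TC users, a significant 60-month difference could arise without any e-cigarette effect. A baseline difference in the other direction could hide a real one. The article expects its results to inform guidelines and regulation.

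**Working it through.** **1. The plan's own figure.** Inputs from Sample size estimation: p1 = 0.20, p2 = 0.30, alpha 0.05 (two-sided assumed), power 80%.

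n = [z(0.975)·√(2·p̄·q̄) + z(0.80)·√(p1q1 + p2q2)]² / (p2 − p1)²
= (1.95996 × 0.61237 + 0.84162 × 0.60828)² / 0.01 = 293.15, so 294.

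With continuity correction: (n/4)·[1 + √(1 + 4/(n·0.10))]² = 73.29 × (1 + 1.0660)² = 312.8, so 313.

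This reproduces the stated 313, which is the size for an unadjusted comparison of two proportions. Dropout alone gives 313/0.80 = 391.25, so 392. The step from 392 to 500 is an unquantified allowance for modelling.

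**2. Room for forced covariates.** 500 × 0.80 = 400 per group. Expected quits in TC plus Mixed at 60 months: 400 × 0.20 + 400 × 0.30 = 200. At 10 events per variable: 200/10 = 20 parameters.

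**3. The crude 60-month test with no group effect.** Simulated: 400 per group, TC rate 20%, one continuous confounder, 1,500 replicates. Its strength and imbalance are assumptions, because the article gives neither.

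| OR per SD | Imbalance | Mixed rate from confounding alone | Fisher p<0.05 |
|---|---|---|---|
| 1.2 | 0.3 SD | 20.9% | 5.2% |
| 1.5 | 0.3 SD | 22.0% | 8.1% |
| 1.5 | 0.5 SD | 23.3% | 18.4% |
| 2.0 | 0.5 SD | 25.6% | 44.5% |
| 2.0 | 0.8 SD | 29.4% | 84.3% |

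The last row almost reproduces the planned 20% against 30%.

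**4. Chance that a confounder passes entry at 0.10.** With D = 200 events and covariate SD s (1 on the SD scale, 0.5 for a 50/50 binary):

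P = Φ(√D·s·ln HR − 1.645) + Φ(−√D·s·ln HR − 1.645)

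For HR 1.1 per SD: √200 × 0.0953 = 1.348, and Φ(−0.297) + Φ(−2.993) = 0.385.

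| HR | Per SD | 50/50 binary |
|---|---|---|
| 1.1 | 39% | 17% |
| 1.2 | 83% | 36% |
| 1.3 | 98% | 58% |
| 1.5 | about 100% | 89% |

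**5. What the screen leaves in the Cox model.** Simulated: 400 per group, no group effect, forward entry at p<0.10 with group, age and gender forced. Cells show group HR / rejection rate; 250 runs per row (Monte Carlo error about 1.5 points near 5%).

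| Confounders (HR per SD, imbalance) | Age, gender, group only | p<0.10 entry | All forced |
|---|---|---|---|
| One (1.5, 0.5 SD) | 1.22 / 25% | 1.00 / 6% | 1.00 / 6% |
| Four (1.3, 0.3 SD) | 1.34 / 47% | 0.99 / 5% | 0.99 / 5% |
| Four (1.1, 0.3 SD) | 1.15 / 16% | 1.07 / 8% | 1.02 / 4% |
| Six (1.1, 0.3 SD) | 1.17 / 16% | 1.03 / 6% | 0.97 / 6% |

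In the last row the forced HR of 0.97 is noise around 1. The selected-to-forced ratio, 1.03/0.97 = 1.06, is the better reading.

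A larger run had six weak confounders all acting in the same direction, with 1,000 replicates per row:

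| log HR per SD, imbalance | Entered | HR after entry rule | Rejects: entry rule | Rejects: all forced |
|---|---|---|---|---|
| 0.10, 0.3 SD | 2.2 of 6 | 1.06 | 8.0% | 4.5% |
| 0.10, 0.5 SD | 2.3 of 6 | 1.10 | 14.4% | 4.9% |
| 0.15, 0.3 SD | 3.9 of 6 | 1.05 | 7.4% | 4.8% |
| 0.15, 0.5 SD | 4.0 of 6 | 1.07 | 10.6% | 4.5% |

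A separate 1,200-replicate run of the same kind, at about 25% cumulative quitting, gave 6.8-15.0% with the entry rule and 4.8-5.4% with all forced. With four confounders acting one way and two the other (exponential regression, 400 replicates), the HR fell to 1.01-1.035 and rejection to 6-10%, against about 4-5% with all forced.

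**The case against.** A reader might infer that cessation is left unadjusted, or that confounding will pass as an e-cigarette effect. The article does not support either reading. Fisher's test is worded as a first look, an adjusted Cox model for cessation follows, and mixed-effect logistic models are to be explored. The mixed models name past traditional smoking exposure as a cluster variable, and stratification is to be considered. The sample size is raised partly to allow for multivariate modelling. Nothing names Fisher's test as the deciding analysis, and the 5% threshold covers the adjusted models equally.

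The screen is also weakest where it matters least. A confounder with HR 1.3 per SD enters about 98% of the time, and with strong or moderate confounders selection matched forcing all of them. The residual bias depends on assumed weak confounders, and its upper end requires them all to act in one direction. A full covariate list is something an article may leave to the full protocol or analysis plan.

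All of this stands, and it limits the size of the point. It does not remove it. The article states a specific selection rule, so this is not a complaint about missing detail. It also leaves open whether the crude or the adjusted result decides, and the logistic models are exploratory only.

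**Conclusion.** The point holds in a limited form. The 0.10 entry rule should not be the means of confounder control for cessation in self-selected groups, and the crude 60-month test should not be able to carry the conclusion.

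The crude test is the larger exposure. With no true effect it rejected between about 5% and 84% of the time over the assumed strengths and imbalances shown. In the Cox model the residual is small to moderate: HR about 1.03-1.10 and false positives about 6-15%, against about 5% with all confounders forced. If confounders partly cancel, the HR bias is smaller still.

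These ranges illustrate assumptions and are not estimates for this cohort, because the article gives no imbalances or confounder effects. Unmeasured confounding remains under either rule.

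**What to change.** For cessation, replace the 0.10 entry rule with a prespecified set forced into the models: age, gender, group, smoking history, education, occupation, marital status, alcohol and physical activity. Two conditions apply.

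- **Baseline cigarettes per day** should be added for TC against Mixed only. EC members smoke no traditional cigarettes at baseline, so the variable is zero for all of them and there is no overlap. For contrasts with EC former smokers, use past smoking exposure instead.
- **Coding** should be coarse, to stay within about 20 parameters at 60 months. As an illustration for TC against Mixed: age 1, gender 1, group 1, smoking history 2, education 2, occupation 2, marital status 1, alcohol 2, physical activity 2, cigarettes per day 1, total 15. The article does not give the coding, so this count is an assumption.

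Make an adjusted 60-month comparison, for example logistic regression with the same set, the deciding analysis, and label Fisher's test descriptive.

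The cost is a few sentences, a few degrees of freedom and slightly wider intervals, with no new data and no larger sample. At earlier time-points there may be fewer quits, and for hospitalisation the article gives no event rate. In both cases the set may have to be smaller under the plan's 10-events rule.

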All outcomes will be self-reported; primary outcome 1 and secondary outcome 2 will be checked using portable CO analyzers, and secondary outcomes 3–7 will be checked using hospital discharge abstracts through a linkage to fiscal codes (for the residents in Abruzzo only). The permission will be granted from each participants and hospitalization data will be provided by the Regional Healthcare Agency of Abruzzo. The admissions for each of the conditions included in the composite outcomes will be defined as follows, based upon the ICD-9-CM principal diagnosis codes in the Italian hospital discharge abstracts (SDO):

– COPD or asthma - 490, 490.0, 491.1, 491.2, 491.21, 491.8, 491.9, 492.0, 492.8, 494, 494.0, 494.1, 496, 493.00, 493.01, 493.02, 493.10, 493.11, 493.12, 493.20, 493.21, 493.22, 493.81, 493.82, 493.90, 493.91, 493.92 [30]

– Myocardial infarction - 410.0-410.9

– Congestive heart failure - 428.0-428.9

– Transitory cerebrovascular ischemia - 435.0-435.9

– Stroke - 433.0-434.9

– Cancer of the lung - 162.0-162.9

– Cancer of the esophagus - 150.0-150.9

– Cancer of the larynx - 161.0-161.9

– Cancer of the oral cavity - 140.0-149.9

– Cancer of the bladder - 188.0-188.9

– Cancer of the pancreas - 157.0-157.9

– Cancer of the kidney - 189.0

– Cancer of the, stomach - 151.0-151.9

– Cancer of the cervix - 180.0-180.9

– Myeloid leukemia - 205.0-205.9

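### In the hospitalization Cox model, adjustment for past cigarette exposure is not guaranteed: it is not a forced term and must pass a p < 0.10 screen within an event budget that the article never estimates

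*Protocol article*

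**What the plan says.** Data analysis, in the protocol article, sets out the model: "Cox proportional hazards analysis will be used to calculate the adjusted relative hazards of traditional smoking cessation (and smoking-related hospitalization) by each variable". It then fixes three rules for building it:

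- Entry of covariates: "Stochastic level of entry into the model will be set at 0.10".
- Forced terms: "with age, gender, and smoking groups forced to entry".
- Size limit: "A minimum events-to-variable ratio of 10 will be maintained in multivariate modeling to avoid overfitting".

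Time interactions and higher-power terms are to be explored for whatever is in the final model.

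Past smoking is not among the forced terms. Data analysis mentions "exposure to past traditional cigarette smoking" only as a cluster variable in additional mixed models that are to be explored. For the EC and Mixed groups it adds "for which also stratification will be considered".

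Interventions and groups says of the EC group: "This group will be further split in the analysis: never or former smokers of traditional cigarettes; smokers of e-cigarettes with or without nicotine". It splits the traditional-cigarette (TC) and Mixed groups once each. Sample size estimation limits EC to former traditional smokers for the cessation comparison. No such limit is stated for hospitalization.

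Admissions are self-reported and checked against discharge records "for the residents in Abruzzo only".

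**The concern.** Past cigarette exposure plausibly influences both which group a person belongs to and the risk of the listed cancers, COPD and cardiovascular admissions. A safety hazard ratio for EC or Mixed against TC is hard to interpret without adjustment for it. Under the rules as written, this variable has no protected place. It can be shut out by the event limit, or dropped because it misses p < 0.10 in a small data set.

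The never-smokers in EC add to the problem: they have no counterpart in TC, so no covariate adjustment makes that part of the contrast comparable.

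Long-term safety is a stated secondary aim, and the Discussion offers the data as a basis for guidelines and regulatory decisions.

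**Working it through.** **What sets the sample size.** Sample size estimation uses cessation of 20% against 30% with 80% power; I take alpha 0.05 as two-sided. The usual two-proportion formula gives [1.96√(2×0.25×0.75) + 0.842√(0.2×0.8 + 0.3×0.7)]² / 0.10² = 293.1, so 294 per group. With continuity correction, (293.1/4)×[1 + √(1 + 4/(293.1×0.10))]² = 313, the article's figure. Dropout gives 313/0.8 = 392, and the article goes to 500 partly to allow for multivariate modelling. For cessation that allowance is ample: TC and Mixed supply 500×0.2 + 500×0.3 = 250 events, or 400×0.2 + 400×0.3 = 200 after dropout. No corresponding count is given for hospitalization.

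**Events the rule requires.** Age (linear) 1 + gender 1 + three-level group 2 = 4 parameters.

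- Forced set: 4 × 10 = 40 events.
- Plus one term for past exposure, or one group split: 5 × 10 = 50.
- Forced set plus all four splits as main effects: 8 × 10 = 80; with past exposure as well, 90.

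**Events to expect.** With N participants, first-admission rate λ per person-year, 5 years of follow-up and 20% exponential dropout (μ = −ln(0.8)/5 = 0.0446):

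events = N × λ/(λ+μ) × [1 − exp(−5(λ+μ))]

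The rate is my assumption, shown as a range, for N = 1500:

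| Assumed rate per 1000 person-years | Expected events | Terms allowed |
|---|---|---|
| 3 | 20 | 2 |
| 5 | 33 | 3 |
| 6 | 40 (39.8) | 3, just short of 4 |
| 7 | 46 | 4 |
| 8 | 53 | 5 |
| 10 | 66 | 6 |

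**Break-even rates** per 1000 person-years, from the same formula. The shares implied by N = 1000 and N = 750 are assumptions:

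| N contributing events | 40 events | 50 events |
|---|---|---|
| 1500, 20% dropout | 6.0 | 7.6 |
| 1500, no dropout | 5.4 | 6.8 |
| 1000, 20% dropout | 9.1 | 11.5 |
| 750, 20% dropout | 12.3 | 15.4 |

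At full N with dropout, 50 events means 50/1500 = 3.3% of those enrolled having a first listed admission. The 80 and 90 events for all splits in one model need about 12.3 and 13.8 per 1000.

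**When the budget is sufficient.** Suppose a true hazard ratio of 1.4 per SD of past exposure (assumed) and 50 events. The expected z is ln(1.4)×√50 = 0.336×7.07 = 2.38. The chance of missing the two-sided 0.10 cut-off is about Φ(1.645 − 2.38) = 23%, and higher if past exposure correlates with age and group.

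**Size of the shift, for illustration.** If groups differ by 0.5 SD in past exposure, with the same hazard ratio of 1.4 per SD, omitting it moves a null group hazard ratio to about 1.4^0.5 = 1.18. Both inputs are assumed.

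**The case against.** A reader might infer that the hospitalization hazard ratio will certainly go unadjusted for past smoking and that the group splits cannot be fitted. The documents do not support that. They give no admission rate, and at 8 to 10 per 1000 with full N there are 53 to 66 events, enough for past exposure or one split. Nor does the article say that all splits enter one Cox model; one at a time needs 50 events.

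It is also tempting to cut N to Abruzzo residents. Linkage there limits checking, while outcomes are self-reported for everyone, so the smaller-N rows are sensitivity cases only. Linkage by fiscal code may even retain people who stop answering questionnaires. Although prior listed disease, angina and antihypertensive medication are excluded, which lowers counts, the composite includes asthma, which is not a listed exclusion.

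Nor can one say that the comparison would mostly reflect lifetime smoking. A shift of 1.18 is modest beside the imprecision: with 33 events, about 22 fall in a two-group contrast, so the 95% limits are roughly the estimate times or divided by exp(1.96×√(4/22)) = 2.3.

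Finally, past exposure is not ignored: it may enter at p < 0.10, and it appears in the exploratory models. Those points stand and narrow the claim. They do not remove it, because none secures the adjustment in the Cox model. Leaving covariate choice to an analysis plan would be normal, but here the article itself fixes the forced set and the entry rule.

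**Conclusion.** The concern holds in a conditional form. The forced terms need 40 events and past cigarette exposure needs 50. With 1500 participants and 20% dropout, these correspond to about 6.0 and 7.6 first admissions per 1000 person-years. Below the second rate the rule excludes the key confounder; below the first it cannot accommodate even the forced terms. Above both, inclusion still depends on a significance screen. Which case applies is unknown, because the article gives no expected rate or count. The thresholds assume one linear term for age, one for past exposure, and events counted in all participants.

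Separately, and at any event rate, the EC group for this outcome may contain never-smokers with no comparable TC participants. The weakness concerns the hospitalization model only; the cessation model has ample events.

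**What to change.** For hospitalization:

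1. State an expected number of first admissions and the rate behind it.
2. Prespecify past cigarette exposure (duration and amount) as an adjustment variable ahead of any covariate chosen by p-value. Each term beyond the first needs a further 10 events.
3. If the event budget does not allow this, adjust through a propensity score or weights for EC, Mixed and TC built on baseline age, gender, past smoking and the other collected covariates. A weighted Cox model with group alone and robust standard errors has two parameters, so the 10-per-variable rule is met from 20 events; age and gender then act through the weights instead of as forced terms.
4. Limit the adjusted EC contrast to former traditional smokers, as Sample size estimation already does for cessation.
5. Treat the splits in Interventions and groups as descriptive for this outcome when events are too few.

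The cost is revised analysis wording and some extra programming, with no new data. Weighting and the restriction lose some precision, and the restriction also lowers the event count. Weighting does not rescue the analysis below about 20 events.

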The enrolment period will last from June to December 2013. Each subject will be requested to compile a structured questionnaire at the time of enrolment at after 6, 12, 24, 36 and 60 months (and eventually, in the case of an expansion of the follow-up, at 84 and 120 months). After the first contact, the follow-up questionnaires will be compiled through a phone interview or through a specifically created website (http://www.ipazienti/fumo), with private password. To reduce potential misclassification, the level of carbon monoxide in expired after breath will be evaluated in all subjects declaring no traditional cigarette smoking in any phase of the follow-up, using portable carbon monoxide analyzers (Smokerlyzer ® piCO + ™, Bedfont Scientific Ltd.). Such an assessment will be made by the investigators, after specific periodical calibration, directly at the home of the participant or at the office of his/her general practitioner. Among the methods to monitor self-reported smoking cessation, also the assessment of cotinine in saliva can be made using portable and relatively economical devices, and such test showed a slightly higher sensitivity/specificity than tests based upon exhaled CO [27]. However, we were not able to find a seller of cotinine portable tests on saliva, and the measurement of breath CO still showed high levels of sensitivity (>90% [27,28]).

Each participant will have to sign a written informed consent. The study protocol has been registered in Clinicaltrials.gov (NCT01785537) and approved by the Ethics Committee of the University of Chieti (Record n. 6; 25-03-2013).

Participants will be enrolled at various study sites within the Abruzzo and Lazio Region using the same standardized procedures.

All the subjects that will be excluded because of past episodes of selected smoking-related major diseases will be requested to participate into a nested case–control pilot study, in which we will collect hospital admission data retrospectively and compare the rates of smoking-related diseases according to the present and past smoking habits.

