### Timetable, participating units and funding

We will start in June, 2013, and the enrolment period will end in December 31, 2013. The preliminary data on outcomes which do not require a first checking through hospital discharge abstracts will thus be available by the end of 2014. A first publication is consequently scheduled for the second semester of 2014, and it will report also the results of the pilot nested case–control study on the subjects that accepted to participate but were excluded from the prospective cohort study because of past episodes of major diseases.

Hospital discharge abstracts are typically available in the Abruzzo region four months after the end of the year. Thus, we plan to obtain the first data on hospitalizations by May 2014, and to finish the data collection by May 2019. The final results of the study will therefore be available at the end of the first semester 2019. Eventually, in case of funds availability and approval by the Ethics Committee, the follow-up could be extended up to ten years.

The following units will participate in the project:

– Department of Medicine and Aging Sciences, University of Chieti (Coordinating unit and sponsor)

– Healthcare Professions Unit, Local Health Authority of Lanciano-Vasto-Chieti (recruitment and data collection)

– University of Turin (recruitment and data collection)

– University Sapienza of Rome (study design and analyses)

– University “Catholic of the Sacred Heart” of Rome (statistical analyses and publication support)

Other institutions and sponsors could be involved during the course of the study. In particular, additional sponsors will be actively searched.

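### At the final analysis, people not followed to an adherence cut-off are dropouts of unknown status, so neither the claimed underestimation of crude adherence nor the censoring correction is secured

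*Protocol article*

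**What the plan says.** The adherence paragraph of the Data analysis section derives secondary outcome 1 at 6, 12, 24, 36 and 60 months. It exempts the 6-month figure, then states that "the crude estimates of adherence for the following time-points would most probably be underestimated". The reason given is that "several participants who are still adherent will be excluded because they will not be followed up to the cut-off point". The remedy is a Nelson-Aalen estimate in which these people are censored and take the failure incidence of the matching period.

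Other sections fix the calendar and the expected losses:

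- Timetable, participating units and funding: "We will start in June, 2013, and the enrolment period will end in December 31, 2013", with a plan "to finish the data collection by May 2019".
- Study design and population: each participant is to "compile a structured questionnaire at the time of enrolment at after 6, 12, 24, 36 and 60 months".
- Sample size estimation: the calculation allows for "an expected 20% rate of withdrawals/dropouts".

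The Background places long-term adherence among the main aims, although the outcome list makes it secondary. It is measured in the EC and Mixed groups.

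**The concern.** The adherence paragraph makes three commitments: a reason why people are not followed, a direction of bias, and one estimator that follows from both. The reason reads most naturally as staggered entry with a closing date that cuts some people short. Such censoring is usually harmless, because entry date seldom bears on the outcome. Dropout is different: whether a person keeps answering may depend on whether that person still uses e-cigarettes.

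If the unfollowed are dropouts, the censored estimate needs an assumption that the article neither states nor supports. Readers are also told in advance that the lower crude figure is the biased one. For a main aim that the Discussion expects to inform guidelines and regulation, that could make a figure look firmer than the data allow.

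**Working it through.** **1. The calendar.** Inputs: last enrolment 31 December 2013; last questionnaire at 60 months; discharge data available four months after year end ("Hospital discharge abstracts are typically available in the Abruzzo region four months after the end of the year").

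- Last 60-month date: 31 December 2013 + 60 months = 31 December 2018.
- Add four months: 30 April 2019. This reproduces the stated close by May 2019.
- The first entrants (June 2013) reach 60 months in June 2018, so all 60-month dates fall between June and 31 December 2018. The earlier visits fall earlier still.

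Calendar censoring at the final analysis is therefore 0% at every time-point.

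**2. Where calendar censoring can occur.** A first report is planned for the second semester of 2014. Assume uniform accrual over the 213 days from 1 June to 31 December 2013.

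- Share with 12 months of potential follow-up on 1 July 2014: 30/213 = 14%.
- On 30 September 2014: 121/213 = 57%.
- On 31 December 2014: 100%.

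Everyone has 6 months by 30 June 2014, and nobody reaches 24 months in 2014. The calendar reason can thus affect the 12-month figure in that report, or a later extension. It cannot explain the final 24-, 36- or 60-month figures.

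**3. Bounds from dropout alone.** Let a be adherence among responders at 60 months (assumed) and 20% the dropout. The lower bound is 0.8a, with no dropout adherent. The upper bound is 0.8a + 0.2, with all adherent.

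- a = 0.4: 32% to 52%.
- a = 0.6: 48% to 68%.
- a = 0.8: 64% to 84%.

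These treat every dropout's status as unknown. Anyone who reported stopping before leaving is a known stopper, which lowers the upper bound.

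**4. Direction.** Illustrative model: true 60-month adherence 50%, constant stopping rate, visits at 6, 12, 24, 36 and 60 months, total dropout 20%. All adherence inputs are assumed.

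With dropout unrelated to adherence:

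- The probability of stopping in an interval of Δ months is 1 − 0.5^(Δ/60): 0.0670 for 6 months, 0.1294 for 12 and 0.2421 for 24.
- Kaplan-Meier, the product of (1 − these) over the five intervals, returns 50.0%.
- The cumulative hazard is 2(0.0670) + 2(0.1294) + 0.2421 = 0.635, and exp(−0.635) = 53.0%.
- Observed adherent at 60 months: 0.5 × 0.8 = 0.400. Stoppers recorded by then: 0.442. A crude figure that keeps known stoppers but excludes adherent dropouts is 0.400/0.842 = 47.5%.

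Other dropout patterns in the same model (%):

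| Dropout pattern | Kaplan-Meier | exp(−Nelson-Aalen) | Crude: adherent among those followed | Crude: adherent dropouts excluded | Non-responders counted as not adherent |
|---|---|---|---|---|---|
| Unrelated to adherence | 50.0 | 53.0 | 50.0 | 47.5 | 40.0 |
| Stoppers leave 3 times as often, only when they stop | 52.9 | 55.5 | 52.1 | 50.1 | 41.7 |
| Stoppers leave 3 times as often throughout | 52.2 | 54.9 | 54.5 | 50.1 | 43.6 |
| Adherent users leave 3 times as often | 48.4 | 51.6 | 46.7 | 45.6 | 37.4 |

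With few, widely spaced visits, exp(−Nelson-Aalen) lies above Kaplan-Meier even without informative dropout (53.0 against 50.0). The effect of dropout itself is the shift from the first row: +1.9 to +2.5 or −1.4 points for Nelson-Aalen, and +2.2 to +2.9 or −1.6 for Kaplan-Meier.

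Over assumed adherence of 30% to 70% and dropout of 10% to 30%, Kaplan-Meier is about 1 to 5 points too high when stoppers leave more often. It is about 0.5 to 3 points too low when adherent users do.

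**The case against.** The adherence paragraph mentions neither entry dates nor a closing date. Its sentence can be read as meaning loss to follow-up, which grows after 6 months, and then it does not conflict with the timetable. That reading is fair, but it leaves the main point standing: the text then describes as still adherent people whose status is unknown once they stop answering.

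On that reading the stated direction can also be right. If dropout is unrelated to adherence, or if adherent users leave more often, the crude figure that excludes adherent dropouts is too low (47.5% and 45.6% against 50%), and censoring moves it towards the truth. This stands. A reader might infer that the correction pushes adherence the wrong way. The documents do not support that as a general statement, because nothing in them says that stoppers leave more often. All groups are followed for traditional smoking, quality of life and hospital admissions, so a person who gives up e-cigarettes still belongs in the study.

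A reader might also infer that the plan takes everyone not followed to be still adherent. It says only that several are, and the estimator gives censored people the later stopping rate of those still observed, not continued adherence.

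Finally, sensitivity analyses are commonly left to a fuller document, and their absence from an article is no finding. That is accepted. The point rests on the premise and the direction of bias that the article does state.

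**Conclusion.** The point holds in a limited form. It is certain from the article's own dates that calendar time cuts nobody short at the final analysis, so the unfollowed are the expected 20% dropouts. The censored estimate then depends on dropout being unrelated to stopping e-cigarettes, which is unsupported, and the claim that the crude figure is too low is not secured.

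The direction of bias is unknown. Its size cannot be derived from the documents, because they give no adherence rate. The bounds of 48% to 68% (20% dropout, 60% among responders) and the modelled errors of a few points are illustrations under stated assumptions. The calendar rationale remains valid for interim reports and for any extension beyond 60 months. This is worth correcting because adherence is a main aim, but it does not invalidate the planned estimator.

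**What to change.** In the adherence paragraph of the Data analysis section:

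- Replace the statement that crude adherence is probably underestimated with one saying that, at the final analysis, censoring before 60 months is loss to follow-up of unknown adherence.
- Limit the calendar rationale to reports issued before all participants reach the time-point, such as the 12-month figure in the 2014 report, or to a later extension.
- Keep the censored estimate as planned. Beside it, report adherence at each time-point with all enrolled EC and Mixed participants as denominator and non-responders counted as not adherent, labelled as a lower bound.
- Give dropout rates by group, and label any stated size of bias as illustrative.

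The cost is a wording change and one extra tabulation, with no new data. The reported adherence will look less favourable or will be shown as a wider range.
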